### Ethics

The Research Ethics and Biosafety Office of University of Western Australia approved the research protocol and procedures of the study (RA/4/1/4790). This trial complies with the principles of the Declaration of Helsinki and all participants will be required to provide written informed consent.

### Intervention

The intervention will consist of eight 30- to 45-minute telephone sessions delivered by a qualified clinical psychologist trained to work in health promotion. These sessions will aim to accomplish the following:promote a positive approach to the menopausal transition through the provision of quality information and building of skills and capacity to manage identified issues;offer verbal and written access to evidence-based information about the MT and its management and, where relevant, depression, anxiety, and about the association between depression and other health issues, such as diabetes, hypertension, lipid abnormalities, and other cardiovascular factors;promote changes in hazardous lifestyle practices associated with increased risk of depression and associated with poor health outcomes (physical inactivity, tobacco smoking, excessive alcohol consumption, and poor nutrition);optimise the management of chronic medical conditions and of depressive symptoms;empower participants by offering access to relevant educational material/health resources and by helping them improve problem-solving techniques and rescheduling of activities; andpromote symptom monitoring and active surveillance of depressive symptoms.

We will post written educational material about the MT, depression and healthy lifestyle practices to intervention participants before their first session. Sessions will take place within 2 weeks of the baseline assessment and again after 2, 4, 8, 12 and 26 weeks [30]. The health promotion officer will use motivational interviewing and problem-solving techniques to address issues that are identified as relevant by the participant (for example, hot flushes or physical inactivity). The intervention will be tailored to the individual needs of each participant, based on the stages of change model and ‘patient-centred’ approach to care [31]. It will also allow for two extra sessions (total equal eight) to be booked if the health promotion officer and the participant identify issues that were not addressed to their satisfaction during the six structured sessions. If no risks or concerns are identified, the intervention will emphasise education. The structure of the sessions described below will be individualised and the content will be delivered according to needs. For example, if significant anxiety or depression is identified these will be dealt with in earlier sessions. The sessions will cover the following areas:During the first session participants will be encouraged to describe their views/experiences of the MT, concerns or troublesome experiences (for example, hot flushes/night sweats, sleep disturbance, loss of social role, prevalent morbidities, change in body composition, symptoms of anxiety/depression, *etcetera*). The Health Coach (HC) will provide information about the physiology of the MT and, if relevant, anxiety and depression. HC will describe common experiences during MT and strategies used to manage undesirable/unpleasant signs/symptoms. Finally, participants, with the support of the HC, will be encouraged to prepare a hierarchical list of troublesome experiences and discuss ways to modify them (for example, lifestyle changes, relaxation techniques). HC and participant will then agree on homework activities. If no major issues are identified, the focus will be on education about the MT;The second session will start with review of homework and feedback. HC will then explain the principles of problem solving using examples from session 1 and from feedback, if available. The participants will be encouraged to prepare list of problems they are currently facing that can and cannot be changed, and will then be asked to select most relevant problem that can be changed, list all possible solutions, and choose the most appropriate one. The session will be completed with the HC encouraging participants to prepare diary of problems and strategies used to mitigate them during the following week.Session three will start with a review of homework and discussion of what did and did not work, as well as ways to get around barriers. HC will then highlight key aspects of a healthy lifestyle, with particular emphasis on physical activity, nutrition, tobacco smoking and use of alcohol. Participants will be encouraged to review how their current lifestyle practices conform to existing guidelines, and then highlight practices that they would like to change. The HC will ask them to prepare hierarchical list of possible changes and strategies to be used, and to consider obstacles, facilitators and outcomes using problem solving techniques.Session four will start with a review of homework and discussion of what did and did not work, as well as ways to get around barriers using problem solving. Participants will then be asked to review their current health problems, how those should be managed and how they are being managed in practice. Difficulties complying with medical advice will be listed, as will be strategies that could optimise health care. The latter will follow the principles of problem solving. Participants will be encouraged to prepare a list of how their health and well-being may be optimised, as well as strategies that could be used to achieve and sustain those changes.Session five will start with a review of homework and discussion of what did and did not work, as well as ways to get around barriers using problem solving. Participants will then be encouraged to describe their understanding of what depression is, as well as its key symptoms and treatment options. The HC will then discuss with participants how to identify the onset of clinically significant depressive symptoms and strategies to respond to their presence appropriately (where/how/why to seek help, who to contact). During the subsequent week, participants will be encouraged to prepare and maintain diary of MT symptoms, lifestyle practices and management of current medical problems as well as active monitoring of depression, including obstacles, facilitators and strategies to overcome them.During the sixth session, the HC will review homework activities and will encourage discussion of what did/not work and ways of getting around obstacles using problem solving. The HC will subsequently provide information about the association between lifestyle practices, MT symptoms, chronic medical diseases and depression, and will review strategies to optimise good MT and minimise the risk of depression. The session will be concluded with a summary of key-points covered during the previous sessions and organisation of up to two additional sessions to address lingering problems or concerns.

Participants who are assigned to usual care (control group) will not have access to the health promotion officer but will take part in the collection of endpoints in the same way as women allocated to the intervention. As for women in the intervention group, clinically significant findings will be communicated to treating GPs.

### Outcomes and study measures

The onset of clinically significant symptoms of depression or of a major depressive episode over 12 months represents the primary endpoint of interest of this trial. We will use the Patient Health Questionnaire (PHQ-9) to establish the presence of clinically significant symptoms of depression. The PHQ-9 is the self-administered depression module of the PRIME-MD diagnostic instrument for common mental disorders. It consists of nine questions about how often the respondent has been bothered by depressive symptoms during the past two weeks, and each item can be scored 0 (not at all), 1 (several days), 2 (a week or more) or 3 (nearly every day). The nine items are as follow: (a) decreased interest or pleasure, (b) low mood, (c) sleep disturbance, (d) lack of energy, (e) disturbed appetite, (f) feelings of failure or guilt, (g) poor concentration, (h) psychomotor disturbance, and (i) suicidal thoughts. The scale has well-established psychometric properties and face-validity, with scores of 15 or greater indicating the presence of clinically significant symptoms of depression that warrant treatment [32]. Endpoints will be collected at 8, 26 and 52 weeks. Another primary endpoint of interest is the onset of a DSM-IV-TR major depressive episode during follow-up, as ascertained by the Mini-Neuropsychiatric Interview (MINI) 8, 26 and 52 weeks after the baseline assessment [33]. The MINI can take between 15 and 45 minutes to complete and it will allow us to investigate the presence of depressive episodes that may have occurred between assessments [34]. Only women who score 15 or more on the PHQ-9 will undergo assessment with the MINI.

Secondary outcomes of interest of this trial include changes in the severity of depressive and anxiety symptoms as measured by the Hospital Anxiety and Depression Scale (HADS) [35], health-related quality of life as measured by the 12-item Short-Form Health Survey (SF-12) [36], severity of menopausal symptoms as measured by the Menopause Rating Scale (MRS) [37], changes in lifestyle as measured by the amount and frequency of alcohol consumed during a typical week, time spent in vigorous and non-vigorous physical activities during a typical week, the Food Frequency Questionnaire [29, 38], weight and height, and use of psychotropic medications. We will also ask participants to disclose the following sociodemographic and clinical data: age, place of birth, education attainment, marital status, number of children and medical history, including information about past diagnosis or treatment for hypertension, diabetes, arthritis, asthma or other chronic respiratory diseases, coronary heart disease, stroke, neurodegenerative diseases (such as Parkinson’s disease), depression and anxiety disorders. Table 1 summarises the assessment schedule of the trial.

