### Women undergoing the menopausal transition require a targeted health promotion intervention

The MT affects all ageing women with intact ovaries. Marked physiological and psychosocial changes characterise this unique period of a woman’s life, including symptoms such as hot flushes and night sweats, remodelling of body shape, shifting social roles (for example, children moving away from home), and onset of chronic illnesses (such as diabetes and hypertension). All these factors may interact to facilitate the development of depressive symptoms during the MT. As depression and poor lifestyle practices in mid life have been associated with poor health outcomes in older age [11, 27–29], developing health promotion interventions that are relevant to women in the MT seem not only desirable, but a necessity.

In summary, published observational data suggest that women undergoing the MT are at increased risk of clinically significant depressive symptoms and highlight numerous health and behavioural factors that might potentially mediate such increased risk. We have designed a health promotion intervention that seeks to address these risk factors systematically and to enhance behaviours associated with good mental health outcomes. More specifically, this study will aim to address the following:determine the efficacy of a telephone-medicated health promotion intervention, compared with usual care, in decreasing the 12-month incidence of clinically significant symptoms of depression in women undergoing the menopausal transition who do not have clinically significant symptoms of depression or mental disorders at the time of entry into the study,determine the efficacy of a telephone-mediated health promotion intervention in decreasing the 12-month incidence of major depressive episodes in women undergoing the menopausal transition, compared to usual care,measure the effect of a telephone-mediated health promotion intervention in decreasing the severity of depressive symptoms over 12 months compared to usual care,ascertain the prevalence of clinically significant symptoms of depression among community-dwelling Western Australian women undergoing the menopausal transition.

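### Twelve-month onset is read from three two-week windows, and the MINI look-back is closed to women below 15 at the visit, so shorter episodes in the coached arm could pass for prevention

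*Protocol article*

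**What the plan says.** The first aim in the Background of the Protocol article is "decreasing the 12-month incidence of clinically significant symptoms of depression". The Outcomes and study measures section then defines the endpoint: "The onset of clinically significant symptoms of depression or of a major depressive episode over 12 months represents the primary endpoint". The same section gives the timing, "Endpoints will be collected at 8, 26 and 52 weeks", and describes the PHQ-9 as asking "how often the respondent has been bothered by depressive symptoms during the past two weeks". It says of the MINI that "it will allow us to investigate the presence of depressive episodes that may have occurred between assessments", and then adds: "Only women who score 15 or more on the PHQ-9 will undergo assessment with the MINI". Table 1 lists the MINI at baseline, 2, 6 and 12 months and shows no such condition.

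Under Intervention, the sessions are to promote "symptom monitoring and active surveillance of depressive symptoms". Session five covers how to identify onset and "strategies to respond to their presence appropriately (where/how/why to seek help, who to contact"). Controls have no access to the health promotion officer. Clinically significant findings are passed to GPs in both arms.

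Use of psychotropic medication is a secondary outcome. Table 1 schedules a medication list and a morbidities checklist at 2, 6 and 12 months.

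**The concern.** Incidence over a year calls for a measurement that can see the whole year. Here the chance that an episode is counted rises with its length, because it must still be present in one of three short windows. If that loss were equal in both arms, it would mainly cost events and power. It need not be equal, because the intervention aims at early recognition and help-seeking, which could shorten episodes.

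Take a woman who becomes depressed at week 12, is treated and scores below 15 at week 26. She is recorded as having had no onset, and the MINI that might have revealed the episode is not given. The protocol recognises the need for look-back and then withholds it from the women for whom it matters.

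At stake is the meaning of the primary result. Shorter episodes are a benefit, but they are not the prevention of onset that the aim states. Nor are they the avoided case on which the Discussion builds its number needed to treat of 13 and its cost per case avoided.

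**Working it through.** **Inputs from the document.** Visits at weeks 8, 26 and 52; two-week recall; 14% against 6%, an 8-point difference (1/0.08 = 12.5, the stated 13); 300 women less 40 lost, so 130 per arm; fifth scheduled session at 12 weeks.

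**Assumptions.** The document gives no episode duration and no effect on duration. I take onset as uniform over 52 weeks, durations as exponential with mean D, and true onset as 14% in both arms, so there is no prevention. The 14% is a prevalence in the Sample size section; using it as 12-month onset is also an assumption. An episode counts if it overlaps any recall window.

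**Coverage.** The windows are weeks 6–8, 24–26 and 50–52: 3 × 2 = 6 of 52 weeks (11.5%). The unobserved stretches are 6, 16 and 24 weeks.

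**Share counted.** An onset inside a window is counted. An onset u weeks before the next window is counted with probability e^(−u/D). Integrating over each stretch:

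share(D) = [6 + D(1−e^(−6/D)) + D(1−e^(−16/D)) + D(1−e^(−24/D))] / 52

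| Mean D (weeks) | Sum in brackets | Share | 14% × share |
|---|---|---|---|
| 8 | 6 + 4.221 + 6.917 + 7.602 = 24.740 | 0.476 | 6.66% |
| 12 | 6 + 4.722 + 8.837 + 10.376 = 29.935 | 0.576 | 8.06% |
| 16 | 6 + 5.003 + 10.114 + 12.430 = 33.547 | 0.645 | 9.03% |
| 24 | 6 + 5.309 + 11.678 + 15.171 = 38.158 | 0.734 | 10.27% |

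**Spurious difference with no prevention.** The last column lets shortening (Dc to Di) begin only with onsets from week 12, when the fifth session falls. The intervention share is then [6 + Dc(1−e^(−6/Dc)) + Dc(e^(−12/Dc)−e^(−16/Dc)) + Di(1−e^(−12/Di)) + Di(1−e^(−24/Di))] / 52.

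| Control vs intervention mean (weeks) | Observed rates | Difference (points) | OR | Difference if from week 12 (points) |
|---|---|---|---|---|
| 24 vs 12 | 10.27% vs 8.06% | 2.2 | 0.77 | 10.27 − 8.48 = 1.8 |
| 16 vs 8 | 9.03% vs 6.66% | 2.4 | 0.72 | 9.03 − 7.13 = 1.9 |
| 24 vs 16 | 10.27% vs 9.03% | 1.2 | 0.87 | 10.27 − 9.27 = 1.0 |

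The range is 1.0 to 2.4 points. At 130 per arm, the differences in the third column would reach two-sided p < 0.05 about 6% to 11% of the time, against 5% by chance.

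**Sensitivity to the model.** A stricter count takes only episodes active on the visit day and fixes the observed control rate at 14%. Halving durations (from 12, 16 or 26 weeks) then gives spurious reductions of about 3.6 to 6.1 points. This is a different model: it supports the direction and shows how far the size depends on assumption.

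**Check on counting treatment as onset.** Suppose equal 14% onset and equal 24-week durations, with 30% of missed episodes treated in the control arm and 60% in the intervention arm (assumed). The missed share is 1 − 0.734 = 0.266. Control: 14 × (0.734 + 0.3 × 0.266) = 11.4%. Intervention: 14 × (0.734 + 0.6 × 0.266) = 12.5%. The bias now runs against the intervention.

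**The case against.** The strongest reply is that the protocol did provide for episodes between visits, through the MINI, and that Table 1 schedules it at every follow-up. That is right as far as it goes. The blind spot exists because of the PHQ-9 condition on the MINI, so this is not a separate problem from that condition. Without it, the protocol's own instrument would largely cover the gaps.

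A reader might infer that shortened episodes will be reported as prevention, or that the primary contrast is biased. The documents do not support that. They give neither episode length nor any effect on it, so the bias is a possibility with a clear direction, not an established fact. The modelled differences seldom produce a significant result by themselves. The week-8 visit is less exposed, because the help-seeking session is by default the fifth, although session content is individualised and depression may be dealt with earlier. GP notification in both arms follows visit findings and does not reach episodes that come and go between visits.

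A reader might also conclude that new treatment or diagnosis should be built into the primary endpoint. Help-seeking is promoted in one arm only, so that would add the opposite bias, as the last check shows.

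Finally, three assessments a year is a legitimate design choice, and sensitivity analyses are often left to an analysis plan that is not shown. That stands: their absence from the article is not the fault. The fault is an incidence endpoint paired with a look-back that the next sentence takes away.

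**Conclusion.** The point holds as a limit on what the primary result can be called. As written, the endpoint captures depression present around weeks 8, 26 and 52. It does not capture 12-month onset, and the look-back that would bridge the two is unavailable to women below 15 at the visit. Because only one arm is trained to recognise onset and seek help, a difference in episode length could appear as a difference in onset, in favour of the intervention. Under the assumed durations and equal 14% onset, that amounts to about 1.0 to 2.4 of the planned 8 points. The direction follows from the text if coaching shortens episodes; the size rests wholly on assumed durations, assumed shortening and the use of 14% as true onset. The matter should be corrected, but it does not invalidate the trial.

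**What to change.** 1. Keep the primary endpoint. Pre-specify a key sensitivity analysis that also counts as a case any woman with newly started antidepressant treatment or newly reported depression since the previous visit. Use the medication list and morbidities checklist already scheduled at 2, 6 and 12 months. New use can be derived by comparison with the previous list. The indication must be recorded, since some antidepressants are started for other reasons.
2. State the downside with it: promoted help-seeking may over-count intervention-arm cases. The primary analysis may favour the intervention and the sensitivity analysis may disfavour it, so read the two together as checks in opposite directions. Neither should act as a veto on the other.
3. Reconcile the MINI look-back sentence, the PHQ-9 condition and Table 1. If the condition stays, describe the outcome as clinically significant depression present at the assessments, not 12-month incidence. Word the prevention, number-needed-to-treat and cost-per-case-avoided statements to match.

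The cost is wording, one added question on indication, a check that the morbidities checklist refers to the interval since the last visit, and one further analysis. If the condition is lifted instead, the cost is interviewer time: at most 300 × 3 = 900 follow-up interviews at the stated 15 to 45 minutes, or 225 to 675 hours before losses.

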**Methods/Design:**

This randomised controlled trial will recruit 300 women undergoing the MT living in the Perth metropolitan area. They will be free of clinically significant symptoms of depression and of psychotic or bipolar disorders. Consenting participants will be stratified for the presence of subsyndromal symptoms of depression and then randomly assigned to the intervention or control group. The intervention will consist of eight telephone health promotion sessions that will provide training in problem solving and education about the MT, healthy ageing, depression and anxiety, and management of chronic health symptoms and problems. The primary outcome of interest is the onset of a major depressive episode according the DSM-IV-TR criteria during the 12-month follow-up or of clinically significant symptoms of depression, as established by a score of 15 or greater on the Patient Health Questionnaire (PHQ-9). Secondary outcomes of interest include changes in the severity of symptoms of depression and anxiety (Hospital Anxiety and Depression Scale, HADS), quality of life (Short Form Health Survey, SF-12), and lifestyle.

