### Sample size

Data from the Australian National Survey suggest that the prevalence of clinically significant depression is 14% around the MT and about 6% immediately before the MT or after the menopause [5]. An effective intervention should decrease the prevalence of depression amongst these women from 14% to 6%, which would represent an absolute risk reduction of 8%. The expected number of women that we will need to treat to prevent one person developing depression is 13. A sample size of 300 women (1:1 allocation) will give the study 80% power to declare such a difference as statistically significant (alpha = 5%). These numbers take into account a loss of 40 women during the course of the study.

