### Statistical methods

Data analysis will be blind to group assignment. We will use descriptive statistics to summarise study measures and will compare their distribution at the baseline assessment for the intervention and control groups using t-tests, Mann-Whitney tests and Pearson’s chi-square statistic. Analyses of outcomes will be intention-to-treat (ITT) and will be ascertained using xtlogit models for binary outcomes (for example, developed a depressive episode during follow up: yes/no. Effect expressed as odds ratio and respective 95% confidence limits) and multilevel mixed-effects linear regression (xtmixed models) to analyse changes in scale scores over time (for example, changes in HADS scores - effect estimate expressed as mean change of score from baseline). We will also use contingency tables to calculate the number needed to treat (NNT) for one person to benefit from the intervention, taking into account the number of participants who may be lost during follow up. The NNT is the reverse of the absolute risk reduction. Alpha will be set at 5% and all statistical tests will be two-tailed. Data from this trial will determine if the intervention causes benefit, harm or neither.

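### The protocol makes major depressive episode both a component of one primary endpoint and a second primary endpoint, with a flat 5% level and no stated decision rule

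*Protocol article*

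**What the plan says.** Four places in the protocol article bear on this.

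- **Abstract, Methods/Design.** One primary outcome, in the singular: "The primary outcome of interest is the onset of a major depressive episode according the DSM-IV-TR criteria during the 12-month follow-up", joined by an *or* to a PHQ-9 score of 15 or more.
- **Outcomes and study measures.** The opening sentence agrees with the abstract. Onset of clinically significant symptoms, "or of a major depressive episode over 12 months represents the primary endpoint of interest of this trial". Later in the same paragraph: "Another primary endpoint of interest is the onset of a DSM-IV-TR major depressive episode during follow-up", with its own instrument (the MINI) and its own visit times. The paragraph closes with a condition: "Only women who score 15 or more on the PHQ-9 will undergo assessment with the MINI".
- **Background, list of aims.** The first aim concerns the incidence of clinically significant symptoms. The second is a separate efficacy aim: "decreasing the 12-month incidence of major depressive episodes in women undergoing the menopausal transition, compared to usual care".
- **Statistical methods.** "Alpha will be set at 5% and all statistical tests will be two-tailed". The article gives no testing order, no division of alpha and no rule on whether one or both endpoints must succeed.

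The Sample size section plans for one binary comparison only, 14% against 6% at alpha 5%.

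**The concern.** A reader cannot tell how many primary endpoints the trial has. If there is one, MDE on its own is secondary and cannot carry the main claim. If there are two, the protocol has to say what counts as success, because two tests at 5% with success on either give a higher overall error rate than one.

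Two things are at stake. The first is the familywise error rate for the primary claim. The second does not depend on any calculation: with both labels in the text, either the composite or MDE alone could be presented as the deciding endpoint once the data are known, and both choices could be defended from the protocol.

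**Working it through.** **Inputs from the article.** Total 300 women, 1:1, less an expected loss of 40: (300 − 40)/2 = 130 per arm. Planned rates are 14% and 6%. Alpha is 5%, two-sided. The MINI is given only at a PHQ-9 score of 15 or more.

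**Input assumed.** The share of PHQ-9 cases that meet MDE criteria is not given. A range of 30% to 90% is used.

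**Step 1: how the endpoints relate.** No MINI is done below a score of 15, so every detected MDE is already a PHQ-9 event. Two things follow. The composite is the same event as a PHQ-9 score of 15 or more, so the first aim and the composite do not compete. And MDE is a subset of the composite, so the two test statistics are positively correlated. (Table 1 lists the MINI at each follow-up without repeating the condition; the explicit sentence in the text is taken as governing.)

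**Step 2: the correlation.** Let C be the composite, with rate pC, and M be MDE, with rate pM = share × pC. Since M lies within C, Cov(M, C) = pM(1 − pC), and

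ρ = √[ pM(1 − pC) / ( pC(1 − pM) ) ].

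At pC = 0.14 and a share of 0.5, pM = 0.07 and ρ = √[(0.07 × 0.86)/(0.14 × 0.93)] = √(0.0602/0.1302) = 0.68.

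**Step 3: the plan's own 5%, for a single test.** The test is the pooled two-proportion statistic z = (p1 − p2)/√[ p̄(1 − p̄) × 2/n ], with n = 130 and rejection at |z| > 1.96. Simulated under no effect, the composite alone rejects in about 4.8% to 4.9% of trials at rates of 6% and 14%. One primary endpoint therefore holds the stated level.

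**Step 4: two primaries, either sufficing.** Chance of at least one two-sided false positive under no effect on either endpoint (1,000,000 simulated trials per cell, 130 per arm):

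| Composite rate | MDE share 30% | 50% | 70% | 90% |
|---|---|---|---|---|
| 14%, normal approximation | 9.0% | 8.4% | 7.7% | 6.6% |
| 14%, simulated | 8.6% | 8.3% | 7.7% | 6.5% |
| 6%, simulated | 8.3% | 7.8% | 7.2% | 6.2% |

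A repeat run, with a 10% rate added, stayed within about 0.1 percentage point of these cells and inside the range 6.2% to 8.6%. If every PHQ-9 case were an MDE, the two tests would coincide and the rate would return to 5%.

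**Step 5: false claims of benefit only.** Under no effect the two directions are symmetric, and nested endpoints almost never reach significance in opposite directions. The benefit-side rate is therefore half the two-sided rate: 6.2%/2 = 3.1% to 8.6%/2 = 4.3%, against a nominal 5%/2 = 2.5%. Direct simulation of the benefit tail gives the same range.

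**Step 6: what each remedy does.** In fixed sequence (composite first, MDE only if the composite is significant), a false primary claim requires the composite to reject, so the rate stays at 5%. A split at 2.5% each gives about 3.3% to 4.6% by normal approximation, but at 130 per arm it lowers power for 14% against 6% from 57.6% to 46%.

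**The case against.** **It may be loose wording.** The abstract and the opening sentence both use the singular, and the outcomes paragraph then goes through the PHQ-9 and the MINI in turn. The disputed sentence could be introducing the second component. That is possible, but the sentence calls MDE another primary endpoint and the aims give it a separate efficacy question. If a component was meant, the text still needs correcting.

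**Multiplicity is commonly left to the analysis plan.** This stands in part. The lack of an order or split is not itself a fault of a journal article. The conflicting labels are in the article, however, and a later plan would have to contradict one of them.

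**The inflation depends on an unstated rule.** This stands. If both endpoints had to succeed, or MDE were tested only after the composite, the error would not exceed 5%. The article states neither, nor does it say that either endpoint suffices.

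**Stronger readings that the article does not support.**

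- A reader might infer that the chance of falsely claiming that the intervention prevents depression exceeds 5%. It does not. The tests are two-tailed, and the benefit side reaches 4.3% at most over the assumed range. The figures above 5% count false harm as well.
- A reader might quote 1 − 0.95² = 9.75% for two independent tests. The MINI condition nests the endpoints, so independence cannot occur.
- A reader might add that MDE alone is badly underpowered. Any figure rests on an assumed MDE rate and is not a multiplicity effect. That 130 per arm gives 57.6% power for 14% against 6%, and not the stated 80%, is a separate matter.

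**Conclusion.** The point holds as an internal contradiction with a modest consequence for the error rate. The abstract, the aims and the outcomes section disagree on whether MDE is a component of one primary endpoint or a second primary endpoint, and this can be read directly from the text.

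The error-rate part is conditional. It requires that success on either endpoint counts, and it rests on an assumed MDE share of 30% to 90%, nested endpoints, 130 per arm and simple two-proportion z-tests in place of the planned xtlogit model. Under those conditions the two-sided rate is about 6.2% to 8.6% against 5%, and the benefit-side rate about 3.1% to 4.3% against 2.5%. The freedom to choose the deciding endpoint after the results does not depend on these figures. This should be corrected, but it does not by itself invalidate the design.

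**What to change.** 1. Keep the composite defined in the abstract as the sole primary endpoint, tested at two-sided 5%. State beside it that, because of the MINI condition, it is the same event as a PHQ-9 score of 15 or more during follow-up.
2. In Outcomes and study measures, relabel MDE as the first secondary endpoint, tested at two-sided 5% only if the primary is significant (fixed sequence). Put the same order in Statistical methods.
3. Align the aims: tie the first to the composite and mark the second as secondary.
4. Record the change as a protocol amendment and in the trial registry, dated, and before any comparison of outcomes by arm.

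The cost is more than editing. The trial is registered and recruiting, so an amendment is needed, and MDE alone can no longer carry a primary claim. No extra participants are needed. Keeping two primaries with 2.5% each would also resolve the conflict, but would raise the requirement for 14% against 6% at 80% power from 220 to 267 evaluable women per arm.
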